### Translational research

Tumour samples will be examined for biomarkers (proteins, DNA and RNA) which might be associated with sensitivity to TMZ and nivolumab. Plasma samples will be examined for ctDNA.

### Contraception

Contraception is mandated from trial entry until at least 5 months (females of childbearing potential) or 7 months (male) following the last dose of study treatment.

Female participants who are of child bearing potential must have a negative serum or urine pregnancy test 24 hours prior to the start of treatment and agree to use two effective forms of contraception, one of which should be highly effective. These must be used from the first administration of study treatment, throughout the trial and for 5 months after last dose of study treatment.

A woman is considered of childbearing potential, i.e. fertile, following menarche and until becoming post-menopausal unless permanently sterile. Permanent sterilisation methods include hysterectomy, bilateral salpingectomy and bilateral oophorectomy. A postmenopausal state is defined as no menses for 12 months without an alternative medical cause. A high follicle stimulating hormone (FSH) level in the postmenopausal range may be used to confirm a postmenopausal state in women not using hormonal replacement therapy. However, in the absence of 12 months of amenorrhea, a single FSH measurement is insufficient.

Female patients must refrain from egg donation from the first administration of the study treatment, throughout the trial and for 5 months after the last dose of study treatment.

Male participants with female partners of child-bearing potential must agree to take measures not to father children by using one form of effective contraception (as above) to be effective from the first administration of all study drugs, throughout the trial and for 7 months after last dose of study treatment. Male participants must also refrain from donating sperm during this period.

Men with pregnant or lactating partners will be advised to use barrier method contraception (for example, condom plus spermicidal gel) to prevent exposure to the foetus or neonate.

## Data collection and management

### Plans for assessment and collection of outcomes

Hospital research staff will enter participant data into the study electronic case report forms (eCRFs) via a remote data collection tool (Medidata Rave). Only trained personnel with specific roles in the study will be granted access to the eCRFs. SCTU trial staff will regularly check the data for missing or anomalous values. Data queries will either be automatically generated within the eCRF, or manually raised with site by the SCTU team. Site staff will respond to explain or resolve the discrepancies.

The PIS and Informed Consent Form will outline the participant data to be collected and how it will be managed or might be shared, including handling of all Patient Identifiable Data (PID) and sensitive PID adhering to relevant data protection law.

### Data management

Participant data will be entered remotely at site and retained in accordance with the current Data Protection Regulations. The PI is responsible for ensuring the accuracy, completeness, and timeliness of the data entered.

The participant data is pseudo anonymised by assigning each participant a participant identifier code which is used to identify the participant during the trial and for any participant-specific correspondence between the SCTU and site. The site retains a participant identification code list, which is only available to site staff.

Only the investigator and personnel authorised by them should enter or change data in the eCRFs. When requested, laboratory data must be transcribed, with all investigator observations entered into the eCRF. The original laboratory reports must be retained by the Investigator for future reference.

Data queries will either be automatically generated within the eCRF, or manually raised by the SCTU, if required. All alterations made to the eCRF will be visible via an audit trail which provides the identity of the person who made the change, plus the date and time.

At the end of the trial, after all queries have been resolved and the database frozen, the PI will confirm the data integrity by electronically signing all the eCRFs. The eCRFs will be archived according to SCTU policy and a PDF copy including all clinical and Meta data returned to the Investigator for each participant.

## Oversight and monitoring

The trial may be subject to inspection and audit by University of Southampton (under their remit as Sponsor), SCTU (as the Sponsor’s delegate) and other regulatory bodies to ensure adherence to the principles of GCP, Research Governance Framework for Health and Social Care, applicable contracts/agreements and national regulations.

Upon receipt of a request from SCTU, the PI will allow the SCTU direct access to relevant source documentation for verification of data entered onto the eCRF (taking into account data protection regulations). Access should also be given to trial staff and departments (e.g. pharmacy). Where on-site monitoring is not permitted due to the COVID-19 pandemic, alternative strategies such as remote monitoring will be deployed. These will be fully described in the trial monitoring plan.

The participants’ medical records and other relevant data may also be reviewed by appropriate qualified personnel independent from the SCTU appointed to audit the trial, including representatives of the Competent Authority. Details will remain confidential and participants’ names will not be recorded outside the trial site without informed consent.

## Statistical analysis

For the primary and secondary objectives, patients who have consented and received at least one dose of nivolumab will be analysed. However, for the exploratory objectives those that have just received TMZ, and not commenced onto nivolumab, will also be analysed.

Response rates (including the primary endpoint) and other categorical data will be presented as percentages with 95% Clopper-Pearson confidence Intervals [37], with continuous data as means and standard deviations or medians and quartiles as appropriate. The primary endpoint will also be presented with a one-sided 90% lower confidence interval limit (to align with the sample size calculation). A secondary analysis will be conducted for the primary endpoint using only those who receive at least two weeks of TMZ (to acknowledge that this subgroup should have been exposed sufficiently for the proposed TMZ mechanisms to have had an impact). Time to event data will be presented in a Kaplan-Meier curve with median survival rates being presented. Waterfall plots will be produced to show changes in tumour size from baseline to treatment assessment time points.

A full and detailed statistical analysis plan will be developed prior to the final analysis of the trial.

All analyses will be carried out using STATA v16 or higher and/or SAS v9.4 or higher.

There are no plans for an interim analysis to be conducted during the ELEVATE trial.

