**Discussion:**

ELEVATE will provide evidence for whether giving nivolumab after temozolomide in patients with previously treated advanced oesophagogastric adenocarcinoma is safe and biologically effective prior to future randomised trials.

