## Objectives

The primary objective is to determine the activity of maintenance TMZ dosing followed by nivolumab treatment to evaluate the potential for a future randomised trial against a standard of care control arm. The rationale to continue TMZ for 3 months or until PD is to evaluate the emergence of Mismatch Repair Deficiency (MMRd) both with and without radiological PD, as clinically relevant MMRd may emerge before radiological progression. This will also reduce the number of patients who drop out due to symptomatic progressive disease.

Secondary objectives include determining the safety of TMZ and nivolumab, the effect of TMZ priming followed by nivolumab on disease control rates, progression free survival (according to RECIST v1.1 and iRECIST criteria), overall survival and safety and toxicity. The quality of life of trial participants will also be assessed using EORT-QLQ-C30, EORT-QLQ-OG25 and EQ-5D-5L questionnaires.

Exploratory objectives include identifying the proportion of patients treated with TMZ that develop MMRd, by comparing pre-TMZ and post-TMZ tumour biopsies. Understanding the relationship between MGMT protein expression, MGMT methylation and acquisition of MMRd, and the rate of increased acquisition of tumour mutation burden after TMZ and the relationship between Tumour Mutational Burden (TMB) acquisition and response to nivolumab will be explored. MGMT immunohistochemistry status after chemotherapy but before TMZ will be characterised. Another objective is to interrogate the response of the tumour microenvironment to immune checkpoint blockade. Tumour evolution of non-MMR genes will also be assessed under chemotherapy using archival, post-chemotherapy and post TMZ biopsies. ctDNA for tumour burden and clonal dynamics will be assessed comparing a baseline sample to post-TMZ and post nivolumab in relation to clinical and radiological response. We will correlate TMB in blood with TMB using Whole Genome Sequencing (WGS).

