### Setting

ELEVATE will be run in 6-8 secondary care hospitals in the UK with the aim of recruiting up to a total of 18 evaluable patients.

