### Sample size and recruitment

The sample size calculation was performed using Sample Size Tables for Clinical Studies. This phase II trial will be based on A’Hern’s single stage design [36]. The primary endpoint of objective response measured in ELEVATE is to nivolumab (following progression, or 3 months without progression, on TMZ), not to TMZ monotherapy, i.e., the baseline measurement for indicating response/progression is taken from the point of initiation of nivolumab.

Based on 10% alpha and 80% power, and assuming a response rate of <10% would not be sufficient activity to warrant further investigation in a future phase III, and a >30% response rate would warrant further investigation in a future phase II, the required sample size is 18. If 4 or more responses are observed in 18 patients then the treatment will be considered sufficiently active to justify its inclusion in a future phase III. The lower limit of 10% ORR was chosen based on this being expected when using nivolumab in unselected populations.

In order to identify 18 MGMT low/methylated patients and based on an estimated minimum 20% showing MGMT loss then, 90 patients will be required to be screened. We anticipate needing to screen approximately 120 patients to account for screen failures and a very small number of deaths in recruited participants prior to starting nivolumab.

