### Withdrawal criteria

Participants are free to withdraw consent from the study at any time without providing a reason. A participant could also withdraw from receiving study treatment but may not wish to withdraw from the trial. In this instance, the participant will be encouraged to attend follow-up visits in accordance with the trial schedule. Should any participant become pregnant during the trial, study treatment will be discontinued.

After the participant has entered the trial, the clinician remains free to give alternative treatment to that specified in the protocol at any stage if they feel that it is in the participant’s best interest, but the reasons for doing so should be recorded. In these cases, participants will be withdrawn from protocol treatment but remain within the trial for the purposes of follow-up and data analysis. All participants are free to withdraw at any time from the protocol treatment without giving reasons and without prejudicing further treatment.

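### The planned secondary safety and overall survival results leave out participants who take temozolomide but never start nivolumab

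*Protocol article*

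**What the plan says.** The Statistical analysis section of the protocol article defines the set: "For the primary and secondary objectives, patients who have consented and received at least one dose of nivolumab will be analysed". The next sentence makes the only exception: "However, for the exploratory objectives those that have just received TMZ, and not commenced onto nivolumab, will also be analysed". No other section names a safety set or an all-treated set.

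The Objectives section lists the secondary aims: "Secondary objectives include determining the safety of TMZ and nivolumab, the effect of TMZ priming followed by nivolumab on disease control rates", followed by progression-free survival (PFS), OS, and safety and toxicity.

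Under Treatment, TMZ is given alone for 3 months or until progression, and nivolumab starts within 3 weeks of that point. A participant who stops TMZ early, for toxicity for example, also moves on to nivolumab.

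The Sample size and recruitment section raises the screening number to "account for screen failures and a very small number of deaths in recruited participants prior to starting nivolumab". For the primary endpoint it states that "the baseline measurement for indicating response/progression is taken from the point of initiation of nivolumab". The Setting section gives the aim as "recruiting up to a total of 18 evaluable patients".

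Under Withdrawal criteria, when the clinician gives a different treatment, "participants will be withdrawn from protocol treatment but remain within the trial for the purposes of follow-up and data analysis".

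**The concern.** A set defined by the first nivolumab dose suits response and PFS, because both are measured from that dose. It does not suit the safety of TMZ, which every participant has been taking for weeks by then. Nor does it describe survival under the whole sequence.

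The omission is selective. Someone who stops TMZ for toxicity but stays fit goes on to nivolumab and is counted. Someone who dies, or becomes too ill to start, is not. Because the recruitment aim counts evaluable patients, early losses are made up in number while their events drop out of the result.

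The abstract says the trial will show whether the sequence "is safe and biologically effective prior to future randomised trials", and the article describes this as the first use of the combination in this population. A secondary safety summary that cannot contain a death before nivolumab is a weak basis for that statement.

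**Working it through.** **1. Is the restriction really stated for safety and OS?** Safety of TMZ and nivolumab, and OS, are secondary objectives (Objectives). Secondary objectives use nivolumab-treated participants only, and TMZ-only participants enter the exploratory objectives (Statistical analysis). The contrast between the two sentences rules out reading the restriction as applying to response alone.

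**2. The plan's own figure.** Single-stage exact binomial design with null rate 10%, target rate 30%, n = 18 and success at 4 or more responses:
- P(X ≥ 4 | n = 18, p = 0.10) = 0.098, against a limit of 10%.
- P(X ≥ 4 | n = 18, p = 0.30) = 0.835, against a requirement of 80%.

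The stated sample size reproduces. It depends only on nivolumab-treated participants, so a wider safety or OS set leaves it unchanged.

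**3. Share left out.** The article gives no number of non-starters. Assume k = 1 to 3 beside 18 treated. The share of TMZ starters left out is k/(18 + k):
- k = 1: 1/19 = 5.3%
- k = 2: 2/20 = 10.0%
- k = 3: 3/21 = 14.3%

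**4. Deaths before nivolumab.** In the planned set this count is 0/18 by construction. If all k non-starters died, the all-TMZ figures with 95% Clopper-Pearson intervals would be:
- 1/19 = 5.3% (0.1% to 26.0%)
- 2/20 = 10.0% (1.2% to 31.7%)
- 3/21 = 14.3% (3.0% to 36.3%)

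**5. Toxicity, illustration only.** Suppose 3 of 18 treated participants had grade 3-4 TMZ toxicity (16.7%, interval 3.6% to 41.4%) and every non-starter did too. The rate becomes 4/19 = 21.1%, 5/20 = 25.0% or 6/21 = 28.6% (the last with interval 11.3% to 52.2%). Both inputs are invented and the intervals overlap widely, so this shows a direction and not a size.

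**6. OS timed from TMZ start.** The planned end of TMZ alone is day 84, which is 12 weeks (Table 1), and nivolumab may start up to 3 weeks later: 12 + 3 = 15 weeks. Each analysed participant has by definition survived to the first nivolumab dose, so up to about 15 weeks of survival is guaranteed.

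For the effect on the median, assume exponential survival with rate λ from TMZ start, and remove the shortest-surviving share d. The median of the rest solves exp(−λt) = (1 − d)/2. Divided by the true median, ln 2/λ, this gives the ratio 1 − ln(1 − d)/ln 2:
- d = 1/19: 1.078, an overstatement of about 8%
- d = 2/20: 1.152, about 15%
- d = 3/21: 1.222, about 22%

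A finite-sample simulation (400,000 trials) gave 1.077, 1.147 and 1.217. If non-starters are a random share, the ratio is 1.00.

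**7. OS timed from nivolumab start.** No survival time is guaranteed, and the ratios in step 6 do not apply. The result describes those who reached nivolumab, and deaths before it are not counted.

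**The case against.** Much of the case on the other side stands.

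- **OS in nivolumab starters is a coherent question.** The objective concerns priming followed by nivolumab, and response and progression are measured from nivolumab start. The article does not give the OS time origin, which a statistical analysis plan may properly settle. A reader might infer that the planned OS is biased upward whatever the origin. The documents do not support that: guaranteed survival and the 8% to 22% range arise only if OS runs from TMZ start.
- **The number affected may be small.** Participants who progress on TMZ or stop it for toxicity still go to nivolumab, and the article expects few earlier deaths. Three non-starters is a generous assumption.
- **Participants are protected.** Adverse events are recorded from the first TMZ cycle, serious events are reported in real time, and the data monitoring committee reviews safety. A reader might infer that TMZ toxicity goes unmonitored or is ignored altogether. It does not: TMZ toxicity in those who later receive nivolumab is also analysed.
- **No decision rests on safety rates or OS.** The only numerical go/no-go rule is 4 responses in 18.

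What does not stand is the reply that the safety set is a detail left for later. The article states the rule, and an analysis plan that follows it inherits the gap. Monitoring protects participants but does not put these events into the planned result.

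**Conclusion.** The safety point holds on the text. As written, the secondary safety result omits toxicity and deaths in participants who took TMZ and never started nivolumab, a group the article itself expects to exist. This should be corrected before the analysis.

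The OS point holds in a limited form. The planned OS covers only those who survived to nivolumab, and its meaning depends on a time origin that is not stated. OS from TMZ start in all TMZ starters is needed beside the conditional summary, not in place of it.

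The sizes are illustrative. They rest on an assumed 1 to 3 non-starters (5.3% to 14.3% of TMZ starters). For the median OS overstatement of 0% to 8-22%, they also rest on OS timed from TMZ start, with random leavers at the lower end, and the shortest survivors and exponential survival at the upper.

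A reader might also infer that the response analysis is compromised. It is not: its baseline is nivolumab start, and the 4-of-18 rule keeps an alpha of 0.098 and a power of 0.835.

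**What to change.** In the Statistical analysis section:

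1. Define a set of all participants who receive at least one TMZ dose. Use it for safety, tabulated by period (TMZ alone; nivolumab with or without TMZ).
2. Report how many never start nivolumab, with reasons, including deaths.
3. State the OS time origin. Present OS from TMZ start in all TMZ starters beside OS from nivolumab start in the nivolumab-treated set.
4. Keep the nivolumab-treated set for the primary endpoint, the 4-of-18 rule and PFS.

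The safety change costs one extra analysis set and no new data, since Table 1 already schedules adverse event collection from the first TMZ cycle. OS needs a small clarification of follow-up. Remote survival follow-up is described as starting after confirmed progression, and Table 1 marks next-treatment details only at progression or end of treatment. Survival follow-up should be stated to cover those who stop after TMZ, in line with the Withdrawal criteria section. Registration with NHS Digital at baseline may help to obtain dates of death.

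The downside is that safety and OS may look less favourable. The sample size does not change.

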## Adverse event reporting and harms

Data on AEs will be collected at treatment and follow-up visits. SAEs will be reported up to 100 days after the last administration of the trial drug to the SCTU safety desk. The trial also has a UK regulatory compliant real-time SAE reporting process to identify serious AEs and suspected unexpected SAEs that could suspend or stop the trial if warranted.

## End of the trial

The end of trial is defined as the last data collection from the last participant in the trial, required to answer the research question. This will be when the last participant concludes their nivolumab treatment, thus completing the trial. Participants will stop nivolumab treatment after progression (per iRECIST criteria), unacceptable toxicity, withdrawal of consent, or the maximum treatment duration of 24 months on nivolumab.

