Endocrine tests: Morning cortisol, ACTH, TSH (Free T3 and Free T4 in case of abnormal TSH)		X				X^j^	
Full blood count		X	X^k^	X^k^	X	X^k^	
Serology – HBV or HCV		X					
ECG^l^		X					
Adverse Events		X	X	X	X	X	X
Concomitant Medication		X^m^	X	X	X	X	X
Patient registered with NHS Digital			X				
Quality of Life Questionnaires^n^			X	X	X	X	X
Details of next treatment							X
TRANSLATIONAL SAMPLES							
Tumour Biopsy (endoscopy)					X		X^o^
Translational blood (ctDNA, Plasma)		X	X	X^p^	X	X^q^	X

^a^Height and weight. Height only required at screening

^b^Temperature, blood pressure, heart rate, respiratory rate, oxygen saturation

^c^If clinically indicated

^d^Assessments performed following RECIST 1.1/iRECIST guidelines as appropriate)

^e^CT scans are required at week 6 and week 12 of TMZ treatment. Assessment of scan should be completed following RECIST 1.1 guidelines

^f^CT scan not required if cessation of TMZ occurs within 4 weeks of the week 6 scan

^g^CT scan at week 6 and week 12 of Nivolumab treatment and then every 12 weeks thereafter until CT scan demonstrates unconfirmed progression, following iRECIST guidelines, then a confirmatory CT scan should be performed 4-6 weeks later

^h^Urea and electrolytes

^i^AST and/or ALT, ALP, bilirubin

^j^Every 6 weeks on nivolumab (TSH, cortisol)

^k^FBC weekly whilst on TMZ

^l^Within 7 days prior to treatment start date

^m^To include all those being taken from 30 days prior to starting trial treatment and during treatment and up to 100 days after last study dose

^n^EORTC QLQ-C30, EQ-5D-5L & QLQ-OG25

^o^Optional endoscopy

^p^At 4-6 weeks from D1 C1 TMZ

^q^At 4-6 weeks from D1 C1 Nivolumab

There will be no dose escalations or reductions of nivolumab allowed. Participants may be dosed no less than 12 days from the previous dose. The infusion will be administered through a sterile, non-pyrogenic, low protein binding in-line filter with a pore size of 0.2-1.2 *μ*m. It will not be administered as an intravenous push or bolus injection. The total dose may be infused directly as a 10 mg/mL solution or can be diluted to as low as 1 mg/mL with sodium chloride 9 mg/mL (0.9%) solution for injection or glucose 50 mg/mL (5%) glucose solution for injection. The infusion will be administered over 30 minutes. After administration the line will be flushed with sodium chloride 9 mg/mL (0.9%) solution for injection or 50 mg/mL (5%) glucose solution for injection.

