### Treatment and follow-up visits

Participants attend hospital appointments for treatment cycles with assessments similar to those performed during screening, plus reviews of adverse events and treatment adherence. The investigator and/or study personnel will phone participants to check for adherence and toxicities to TMZ, and participants will also have weekly FBC. The time schedule of enrolment, interventions, assessments, and visits for participants are fully detailed in the schedule of events (Table 1). Participants completing the trial, defined as progression on nivolumab (following iRECIST criteria), unacceptable toxicity, withdrawal of consent, or the maximum treatment duration of 24 months on nivolumab, will be managed by standard clinical care from their usual treating clinician. Following confirmed progression patients will be followed up remotely every 4 weeks (via a patient notes check or phone call if required) for details of next treatment and survival until the last participant has completed the study.

Serious adverse event reporting occurs in real-time to the SCTU safety desk throughout the study. Serious adverse events are assessed to determine whether they are related to drug treatment and unexpected or not, and subsequently reported to both Bristol Myers Squibb and the UK regulatory bodies.

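### The trial ends on the day the last participant stops nivolumab, which contradicts its own 100-day safety window; follow-up after a stop without progression is inconsistently described

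*Protocol article*

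**What the plan says.** **End of the trial.** This section contains two statements. The general one is "The end of trial is defined as the last data collection from the last participant in the trial, required to answer the research question". The operational one is "This will be when the last participant concludes their nivolumab treatment, thus completing the trial".

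**Safety window.** Adverse event reporting and harms states: "SAEs will be reported up to 100 days after the last administration of the trial drug to the SCTU safety desk". Footnote m of Table 1 has concomitant medication recorded "during treatment and up to 100 days after last study dose".

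**Follow-up after treatment.** Treatment and follow-up visits lists who has finished: "Participants completing the trial, defined as progression on nivolumab (following iRECIST criteria), unacceptable toxicity, withdrawal of consent, or the maximum treatment duration", the maximum being 24 months on nivolumab. These participants pass to their usual clinician. It then adds: "Following confirmed progression patients will be followed up remotely every 4 weeks", "for details of next treatment and survival until the last participant has completed the study".

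**Participants taken off treatment.** Under Withdrawal criteria, when the clinician chooses another treatment, "participants will be withdrawn from protocol treatment but remain within the trial for the purposes of follow-up and data analysis". Those who leave treatment but not the trial are encouraged to keep attending scheduled visits.

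**Schedule.** The last column of Table 1 is the progression or end-of-treatment visit. It has no CT entry and no later visit follows it. Footnote g, attached to the nivolumab-cycle column, continues CT every 12 weeks until a scan shows unconfirmed progression. Table 1 also registers patients with NHS Digital at baseline, without stating why.

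**The concern.** Safety is one of the questions the trial is meant to answer, and the article says this combination has not been used in this population before. Events that appear after nivolumab stops are part of that answer, which is presumably why a 100-day window was set. An end of trial on the day treatment stops leaves the status of that window open for the participants who finish last: sites could close while reports are still due.

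Overall survival and progression-free survival are secondary endpoints, to be shown as Kaplan-Meier curves with medians. If follow-up ends when someone stops for toxicity, the censoring may be related to prognosis, and the curve may no longer describe the treated group fairly. With 18 participants, each one is 1/18 = 5.6% of the sample. The text also leaves room for sites to act differently: one section counts a toxicity stop as completion of the trial, while another keeps participants who are off treatment under follow-up.

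**Working it through.** **1. The plan's own figure.** Sample size and recruitment gives n = 18 and success at 4 or more responses, with 10% against 30%, alpha 10% and power 80%. By the exact binomial:

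- Alpha = P(X ≥ 4 | 18, 0.10) = 1 − 0.9018 = 0.0982.
- Power = P(X ≥ 4 | 18, 0.30) = 1 − 0.1646 = 0.8354.
- With n = 17 and the same cut-off, power is 0.798, below 80%. A search over smaller n finds none that meets both limits.

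The stated design reproduces, and nothing below changes it.

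**2. The safety window, side by side.**

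| Item | Days after last dose |
|---|---|
| SAE reporting (Adverse event reporting and harms) | 100 |
| Concomitant medication (Table 1, footnote m) | 100 |
| Trial still open for the last participant to stop nivolumab (End of the trial) | 0 |

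If a participant's last nivolumab dose falls d days before the last participant stops, the part of the window inside the trial is min(d, 100) days. For the last participant d = 0, so 0 of 100 days are covered. Anyone with d < 100 has an incomplete window. At least 1 of 18 (5.6%) is therefore always affected. The section also conflicts with its own general definition, because data the protocol requires are still outstanding when nivolumab stops.

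**3. How many participants? An illustration.** The documents give no treatment duration, so the median is an assumption and was varied. Inputs: 18 participants; starts uniform over the 18-month recruitment period (Trial status), ignoring the temozolomide lead-in; exponential nivolumab duration capped at 24 months; trial end at the last stop; 100 days = 100/30.4375 = 3.29 months; 20,000 simulated trials per row.

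| Assumed median duration (months) | Mean number with incomplete window, of 18 | 5th to 95th percentile | Mean number reaching 24 months |
|---|---|---|---|
| 2 | 2.7 | 1 to 6 | 0.005 |
| 3 | 2.1 | 1 to 5 | 0.07 |
| 4 | 1.8 | 1 to 4 | 0.3 |
| 6 | 1.7 | 1 to 3 | 1.1 |
| 9 | 1.9 | 1 to 4 | 2.8 |

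**4. Survival and progression follow-up by reason for stopping nivolumab.**

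| Reason | Counted as completing? | Remote check stated? |
|---|---|---|
| Confirmed progression | Yes | Yes, until the last participant completes |
| Unacceptable toxicity, no progression | Yes | No |
| 24 months, no progression | Yes | No |
| Clinician gives another treatment | Not listed | Kept in follow-up, form not stated |

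Withdrawal criteria does not fill the two empty rows. It refers to visits on the trial schedule, and that schedule shows none after the end-of-treatment visit. If the last participant stops because of progression, that progression also completes the trial, so the remote check for that person has zero length.

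**The case against.** The strongest reply concerns survival data. Completing the trial cannot mean that data collection ends, because participants with progression also complete, pass to usual care and are still checked every 4 weeks. The trigger is confirmed progression, not progression on treatment, so someone who stops for toxicity and progresses later could come under it. Withdrawal criteria keeps participants who are off treatment in follow-up, NHS Digital registration might supply deaths, and footnote g can be read as continuing scans until progression. The analysis plan, which is not shown, would set the censoring rules. An article also condenses the full protocol, which may set out follow-up by reason for stopping.

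Much of this stands. A reader might infer that overall and progression-free survival are lost for every toxicity stop. The documents do not support that: they describe follow-up inconsistently, and no passage says these times are censored at the stop. A reader might also put a number on the affected survival times by assuming a rate of toxicity stops, but the documents give no such rate. Nor does late enrolment by itself mean no survival follow-up: on the natural reading the trial closes with the last person to stop nivolumab, so a late entrant who progresses early is followed until then. Censoring at trial closure is administrative.

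The reply does not reach the safety window. That conflict lies between statements the article itself makes, so condensation does not explain it. Nor does it settle follow-up before any later progression: the purpose of the NHS Digital registration is not stated, and footnote g belongs to the on-treatment column.

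**Conclusion.** The end-of-trial rule contradicts the two 100-day windows and its own general definition. This follows from the text and needs no assumption: the last participant has none of the 100 days inside the trial, and every participant whose last dose falls in the final 100 days has a shortened window. The average of about 1.7 to 2.7 of 18 affected rests on assumed median durations of 2 to 9 months and only illustrates the scale.

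Follow-up after a stop without progression is inconsistently stated across Treatment and follow-up visits, Withdrawal criteria and Table 1. The consequence is a risk of early and possibly informative censoring of two secondary, descriptive endpoints. Its size cannot be computed from the documents.

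The response endpoint, the 4-of-18 rule and the sample size are untouched. This should be fixed, because required safety data fall outside the stated end of trial, but it does not threaten the primary conclusion.

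**What to change.** 1. Define the end of trial as no earlier than 100 days after the last participant's last dose of trial drug.
2. Start the existing 4-weekly remote check when nivolumab treatment ends for any reason except full withdrawal of consent. Record serious adverse events to day 100, progression from routine scans, next treatment and death.
3. Reconcile Withdrawal criteria, Treatment and follow-up visits, Adverse event reporting and harms, End of the trial, and Table 1, so that completing treatment and leaving follow-up are separate events.

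Two further steps are not needed for this correction. A fixed minimum survival follow-up would be a sponsor's choice. Survival follow-up of participants who never start nivolumab would serve no stated secondary analysis, because Statistical analysis limits the primary and secondary objectives to those with at least one nivolumab dose.

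The cost is a protocol amendment, a few more months of notes checks or calls for at most about 18 people, and slightly later final reporting. No extra visits or scans are required. The change is best made before the trial closes, since events not collected prospectively may be hard to recover afterwards.
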